### Study Aims

The primary aim of this study will be to determine the effectiveness of the evidence-informed mobile phone app for smoking cessation, Crush the Crave, on reducing smoking prevalence among young adult smokers after 6 months. Crush the Crave was developed by an expert team based at the University of Waterloo who worked with a technology development team to design, prototype, evaluate, and revise the program over the course of 2 years. This study will represent the first full trial of the program as part of a population-level intervention. We expect that individuals randomized to the evidence-informed mobile phone intervention condition will have higher 30-day point prevalence quit rates than individuals assigned to the control condition after 6 months.

Secondary aims of this study include the following:

1. Examine more proximal outcome measures of cessation behavior, including 7-day point prevalence abstinence (PPA), time to cessation, the number of quit attempts, and the reduction in consumption of cigarettes.

2. Examine satisfaction and patterns of app use at 3 and 6 months, including the extent to which it promotes the use of established smoking cessation services, such as nicotine replacement therapy, health professional consults, medications, and quitline counseling.

3. Examine mediators of cessation outcomes between conditions, such as frequency of app use, use of cessation services, quit intentions, nicotine withdrawal, and the following psychosocial mediators: beliefs and attitudes, stress, social norms, self-efficacy, and perceived social support.

4. Compare the cost-effectiveness of the intervention and control conditions.

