### Sample Size and Power Calculations

Sample size calculations are based on a superiority trial [66,67] and are focused on the difference in the objective measure of the primary outcome event—30-day point prevalence abstinence from smoking—between intervention and control groups. Assuming a ratio of 1:1 for intervention to control subjects, an alpha of .05, power of 80%, and an effect size equal to a 50% increase in self-reported abstinence—17% in the intervention versus 11% in the control condition—the required sample size is 524 per group, for a total of 1048 participants using a two-tailed test on proportions [68]. The 50% increase in effect is reasonable and conservative based on trials of interventions using other mobile and Web-based technologies [41,69,70]. The estimated 11% abstinence rate in the control condition is based on the Ontario Tobacco Survey young adult smokers cohort study where in a sample of 592 young adult smokers, 68 (11.5%) were abstinent at the 6-month follow-up [71]. The 11% abstinence rate is what is expected to occur with a standard self-help condition and is similar to other trials that have tested the effect of self-help materials, with validated 6-month cessation rates of 5% to 15% [50,51]. Based on the experience of similar interventions [41,69], an overall estimate of 20% attrition translates into quit rates of 8.8% in the control condition and 13.6% in the intervention. Therefore, the total sample size required for each group is 677, for a total of 1354 participants.

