The Preacher and Hayes bootstrapping method will be used to provide point estimates and confidence intervals to assess the significance or nonsignificance of a mediation effect, as it provides an increase in power and does not require the normality assumption to be met [72]. The mediation analyses will proceed by first estimating the difference in the outcome variable between the treatment and control groups, adjusting for age and sex as necessary, and then estimating the difference between the conditions for the mediating variables using bootstrapping. Finally, mediating variables and the treatment group indicator, along with covariates, will be entered into models for the primary and secondary responses. This will allow for an investigation of the role the mediators play in accounting for the differences between conditions. For example, use of e-cigarettes, higher levels of dependence, lower levels of self-efficacy, and low perceived social support might mediate quit success, for example, lower quit rates (see Figure 3). Additional secondary analyses will look at models for the response variables involving a treatment group indicator, covariates, and interactions between covariates and the treatment group indicator. These models will examine whether the relationships between the outcome and covariates differ between the conditions. They will also help to identify potential mechanisms, for example, frequency of app usage, by which the intervention might be operating. Statistical analyses will be performed using SAS version 9.4.

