Common criticisms have been made regarding mHealth research designs and trial descriptions [76]. Few large samples and adequately powered randomized controlled trials have been completed to date and many of those that have been done are of short duration and do not fully describe or assess the implementation of the mobile phone intervention. The Crush the Crave trial has been developed to address these concerns with a rigorous design, large sample size, 3- and 6-month follow-up periods, and attention to monitoring the process of implementation and utilization of the intervention. This will allow for sufficient explanation so that others can replicate the intervention [38]. As mHealth technology evolves rapidly, the Crush the Crave trial will allow researchers and policy makers to know which aspects of the intervention worked and which did not [77]. In addition, the development of Crush the Crave involved the target audience and it has been suggested that engaging the users of mHealth interventions is a contributing factor to their adoption and success [78].

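### Frequency of app use is planned as a between-condition mediator although only one arm is given the app, so the mediation test can show a mechanism when the app has no effect

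*Protocol article*

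**What the plan says.** In Study Aims, the third secondary aim of the protocol article is to "Examine mediators of cessation outcomes between conditions, such as frequency of app use, use of cessation services, quit intentions, nicotine withdrawal", followed by psychosocial mediators. App use comes first in that list.

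Statistical Analysis gives one procedure for all mediators, with bootstrap confidence intervals to judge significance. The outcome is compared between arms, then the mediator is compared between arms, and finally "mediating variables and the treatment group indicator, along with covariates, will be entered into models for the primary and secondary responses". Age and sex are named as adjustments for the first step; the covariates of the last step are not listed. The same section then describes models with interactions between covariates and treatment group, and says of them: "They will also help to identify potential mechanisms, for example, frequency of app usage, by which the intervention might be operating".

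The app goes to the intervention group (Study Intervention, Overview) and a print-based guide to the control group (Standard Self-Help Condition). App use is recorded as time-stamped events inside the app (Process Measures). The follow-up questionnaire asks both groups about their use of the app or the guide, which is a different variable in each arm.

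The Discussion (Principal Findings) says that the trial "will allow researchers and policy makers to know which aspects of the intervention worked and which did not".

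**The concern.** A between-condition mediation analysis needs a mediator that can vary in both arms. App use can vary in only one. The comparison of app use between arms is then certain to differ, and it says nothing about whether the app works. All the evidence on whether use leads to abstinence comes from comparing heavier with lighter users inside the app arm. Those people chose how much to use the app, so randomisation does not protect the comparison. More motivated smokers may both use the app more and quit more, and people who relapse may stop opening it.

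At stake is the explanatory claim of the trial. App use could be reported as the mechanism of an app that had no effect on quitting, and the statement about which aspects worked could be built on that result.

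**Working it through.** **1. The plan's own figures.** The sample size is the base for the simulation, so it was reproduced first. Inputs from Sample Size and Power Calculations: two-sided alpha 0.05, power 80%, 1:1 allocation, "17% in the intervention versus 11% in the control condition". With the pooled-variance formula,

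n = [1.96·√(2·p̄(1−p̄)) + 0.8416·√(p₁(1−p₁) + p₂(1−p₂))]² / (p₂−p₁)²

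- 11% v 17%, p̄ = 0.14: (0.9618 + 0.4114)² / 0.0036 = 523.8, so 524 per group. The article says "the required sample size is 524 per group, for a total of 1048 participants using a two-tailed test on proportions".
- The article then states that "an overall estimate of 20% attrition translates into quit rates of 8.8% in the control condition and 13.6% in the intervention" (0.8 × 11% = 8.8%; 0.8 × 17% = 13.6%). With p̄ = 0.112: (0.8741 + 0.3743)² / 0.002304 = 676.4, so 677 per group, as stated.

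Both figures reproduce. Nothing below changes them.

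**2. What the mediation model estimates.** Let A be arm (1 = app), M app use and Y abstinence. The planned outcome model, before covariates, is logit P(Y=1) = β₀ + β₁A + bM. With M = 0 in every control:

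- Controls: logit P = β₀. They carry no information on b.
- App arm: logit P = (β₀ + β₁) + bM. So b is the slope of abstinence on use within the app arm.
- Path a = mean use in the app arm − 0, which is positive by design.

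The test of the indirect effect a·b is therefore a test of whether heavier users quit more often.

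**3. Interaction.** In controls A×M = 0 = M; in the app arm A×M = M. The two columns are identical. The design matrix [1, A, M, A×M] has four columns and rank 3, so a use-by-arm term cannot be separated from use.

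**4. How often a false mechanism appears.** Simulation with 677 per arm and no app effect for anyone. An unmeasured standard normal trait (motivation, say) shifts the log odds of quitting by g per SD and has correlation ρ with latent app use. The model is abstinence on arm and use, with no covariates. A 95% Monte Carlo interval is formed for a·b, with 1000 runs per setting. The values of g and ρ and the shape of the use distribution are assumptions; none is in the article. Share of trials with a significant indirect effect (two-sided, nominal 5%):

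| g | ρ | 11% quitting | 8.8% quitting |
|---|---|---|---|
| 0 to 1.0 | 0 | 4% to 6% | 4% to 7% |
| 0.3 | 0.3 | 11% | 11% |
| 0.3 | 0.5 | 21% | 22% |
| 0.5 | 0.3 | 20% | 19% |
| 0.5 | 0.5 | 50% | 45% |
| 0.8 | 0.3 | 44% | 38% |
| 0.8 | 0.5 | 87% | 82% |
| 1.0 | 0.3 | 58% | 52% |
| 1.0 | 0.5 | 96% | 91% |

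A percentile bootstrap (200 runs, 200 resamples, 11% quitting) gave 21% at g = 0.5, ρ = 0.3, and 5.5% with no shared cause. With a skewed use distribution (11% quitting) the rate was 44% at g = 0.5, ρ = 0.5, and 36% at g = 0.8, ρ = 0.3.

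The false indirect effect is offset by a false direct effect of opposite sign. At g = 0.5, ρ = 0.5 and 11% quitting, the means were +0.50 and −0.52 on the log-odds scale, a sum of −0.02. The test of the randomised contrast stayed near its nominal level, at 2.8% to 6.6% over the 1000-run settings.

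**5. One-sided rates and covariates.** Counting only a positive, significant use coefficient (nominal 2.5%) at 8.8% quitting, the rate was about 2% with no shared cause and 11% to 39% for g of 0.3 to 0.5 with ρ of 0.3 to 0.5. Adjusting for a baseline proxy for motivation lowered this to 7% to 22%. How far it falls depends on how well the proxy captures the trait, which is again an assumption.

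**The case against.** The strongest objections concern how far the point reaches.

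- **The structural zero alone does no harm.** This is correct: with no shared cause the error rate is nominal. The false mechanism needs a common cause of use and quitting, or reverse causation. A reader might infer that the trial would probably report app use as a mediator even if the randomised result is null. The article does not support that. Higher rates follow if use is taken to be almost a proxy for motivation: at a correlation of about 0.82, 52% and 92% for log odds ratios of 0.3 and 0.5. Nothing in the article justifies that assumption.
- **Covariates are planned.** Also correct. Baseline dependence, quit intentions and self-efficacy are collected and could enter the outcome model. They reduce the problem, but the list is not fixed and proxies do not remove the excess.
- **The interaction wording is loose.** A reader might infer that a use-by-arm term is specified. The article offers app usage only as an example of a mechanism that those models help to identify. The rank problem applies only if such a term is meant. The article also does not say that controls are blocked from the app. A few crossovers would make the term estimable in form without removing the confounding.
- **Timing of the other mediators.** A reader might infer that mediators are taken at 6 months, when they may be results of quitting. The questionnaires are given at 3 and 6 months and the mediation text fixes no wave, so this is not a stated error.
- **The claim about which aspects worked has other support.** Event logs and about 40 interviews also bear on it, so only its use-based part is affected.
- **An article condenses.** True, but here the article positively names app use as a between-condition mediator. That is a stated choice and not an omitted detail.

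**Conclusion.** The point holds for frequency of app use as a between-condition mediator. That the first path is non-zero by design, and that the second comes only from non-randomised variation in use, follows from the allocation of the app and needs no assumption beyond no app use among controls.

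The size does need assumptions. The one-sided false-positive rate for a mechanism is about 2% with no shared cause, roughly 10% to 40% under moderate confounding (log odds ratio 0.3 to 0.5 per SD, correlation 0.3 to 0.5), and 80% or more under strong confounding (0.8 to 1.0 per SD, correlation 0.5). Covariate adjustment lowers it. The supported conclusion is that the analysis can show a false mechanism, not that it probably will.

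This concerns a secondary aim. The primary intention-to-treat test and the sample size stand, and the randomised comparison would be visible beside any indirect effect, although the plan does not make the mediation analysis conditional on it. The change should be made before the mediation analysis is run.

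**What to change.** Remove frequency of app use from the between-condition mediation models in the third secondary aim and in Statistical Analysis, and from any use-by-arm interaction. Report it within the app arm only, as time-stamped use before 3 months against 6-month abstinence. Adjust for baseline dependence, intention to quit and self-efficacy, and label the result associational. The label is essential, because early use can still reflect early relapse or unmeasured motivation. In the Discussion, limit the statement about which aspects of the intervention worked accordingly wherever it rests on use.

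The cost is wording and a modest amount of programming. The use logs, the baseline measures and the 6-month outcome are all in the planned data collection, and the sample size does not change. The downside is a more modest claim about mechanism.

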**Figure 3 figure3:**
[figure not shown]
Mediation model. Conceptual diagram depicting Intervention (X), Outcome (Y), and Mediator (Z) variables, as well as hypothesized relationship (a), action (b), and outcome (C') pathways for examination in the mediation analyses.

#### Economic Analysis

The lifetime incremental costs and benefits of the Crush the Crave mobile phone app added to current practice will be estimated from a government perspective using a Markov model adopted in previous economic evaluations of smoking cessation interventions [73]. All costs associated with development of the app and research will be excluded. The costs of delivering the intervention will be assessed by measuring and valuing the incremental resources used [73], including the costs of app maintenance (eg, costs to maintain the server and keep the app working on new operating systems) and the cost of the moderator for the social networking component. A number of brief questions will be included in the follow-up questionnaire concerning the use of NRT, quitlines, and other cessation services to ascertain these costs. Following a methodology proposed by Drummond et al [74], cost-effectiveness will be measured in terms of cost per quitter (6-month continuous abstinence—30-day point prevalence), cost per life year gained, and cost per quality-adjusted life year (QALY) gained for smoking-related diseases—lung cancer, stroke, myocardial infarction, chronic obstructive pulmonary disease, and coronary heart disease—between the intervention and control groups. The incremental cost-effectiveness ratio will also be measured in a manner similar to other studies [75]. To account for the timing of events, costs and consequences will be discounted at 3% [74]. To ensure the robustness of our cost-effectiveness estimates, we will conduct multivariate sensitivity analysis using Monte Carlo simulation. Key input parameters to be examined will include, but will not be limited to, discount rate, intervention costs, quit rates, and unit costs of smoking-related diseases.

## Results

This trial is currently open for recruitment. The anticipated completion date for the study is April 2016.

## Discussion

### Principal Findings

The Crush the Crave trial will evaluate a comprehensive evidence-informed mobile phone intervention for reducing smoking prevalence among a large sample of young adult smokers. To the best of our knowledge, this is one of three published mHealth protocols to assess the effect of a comprehensive and evidence-informed mobile phone app for smoking cessation, and one of the first to evaluate the impact of mHealth smoking cessation self-management on a large sample of young adult smokers. At the time of writing, there were eight trials underway regarding smoking cessation and mobile phone apps (ClinicalTrials.gov) and only two studies that have published findings on the effect of mobile phone-delivered smoking cessation interventions [27,35]. Bricker et al [27] conducted a double-blind randomized trial with a small sample of adult smokers on a theory-based mobile phone app as the intervention versus the National Cancer Institute’s smoking cessation app as the control and found overall quit rates of 13% in the intervention condition versus 8% in the control condition. Conversely, Buller et al [35] compared a mobile phone app with SMS text messaging for a small sample of young adult smokers. They found that the mobile phone app intervention was feasible for delivering cessation support but did not appear to move smokers to quit as quickly as SMS text messaging. The large sample of young adult smokers participating in the Crush the Crave trial will allow for a determination of what factors mediate quitting success through the use of an evidence-informed mobile phone app. In addition, it is one of very few studies to our knowledge that considers the cost-effectiveness of an mHealth intervention for smoking cessation among young adults [75].

Common criticisms have been made regarding mHealth research designs and trial descriptions [76]. Few large samples and adequately powered randomized controlled trials have been completed to date and many of those that have been done are of short duration and do not fully describe or assess the implementation of the mobile phone intervention. The Crush the Crave trial has been developed to address these concerns with a rigorous design, large sample size, 3- and 6-month follow-up periods, and attention to monitoring the process of implementation and utilization of the intervention. This will allow for sufficient explanation so that others can replicate the intervention [38]. As mHealth technology evolves rapidly, the Crush the Crave trial will allow researchers and policy makers to know which aspects of the intervention worked and which did not [77]. In addition, the development of Crush the Crave involved the target audience and it has been suggested that engaging the users of mHealth interventions is a contributing factor to their adoption and success [78].

### Limitations

A limitation of this study is the lack of an effect size for the control group self-help condition for determining sample size. However, systematic reviews and RCTs of printed self-help interventions for young adult populations support the effect size estimate chosen [48-51].

### Conclusions

It is evident that the young adult population of smokers is interested in mHealth technology for helping them quit smoking [24]. If the proposed trial finds support for effective delivery of smoking cessation interventions via mobile phone apps to help young adults quit, it would provide evidence to move forward and include technology-based interventions as part of existing smoking cessation efforts made by health care providers. It would also inform the development of future apps, provide a deeper understanding of the factors that drive change in smoking behavior, and improve the design of existing apps. This study will provide data on the potential of including mHealth technology in population-based smoking cessation interventions as a strategy to economically and effectively reach young adults, and ultimately reduce the prevalence of smoking in this age demographic.

## Abbreviations

NRT: nicotine replacement therapy
PPA: point prevalence abstinence
QALY: quality-adjusted life year
RCT: randomized controlled trials
SMS: short message service
